## Abstract

**Background:**

It is a priority to achieve an adequate nutritional status of iodine during pregnancy since iodine deficiency in this population may have repercussions on the mother during both gestation and post partum as well as on the foetus, the neonate and the child at different ages. According to the WHO, iodine deficiency is the most frequent cause of mental retardation and irrreversible cerebral lesions around the world. However, few studies have been published on the nutritional status of iodine in the pregnant population within the Primary Care setting, a health care level which plays an essential role in the education and control of pregnant women. Therefore, **the aim of the present study **is: 1.- To know the hygiene-dietetic habits related to the intake of foods rich in iodine and smoking during pregnancy. 2.- To determine the prevalence of iodine deficiency and the factors associated with its appearance during pregnancy.

**Methods/design:**

We will perform a cluster randomised, controlled, multicentre trial. Randomisation unit: Primary Care Team. Study population: 898 pregnant women over the age of 17 years attending consultation to a midwife during the first trimester of pregnancy in the participating primary care centres. Outcome measures: consumption of iodine-rich foods and iodine deficiency. Points of assessment: each trimester of the gestation. Intervention: group education during the first trimester of gestation on healthy hygiene-dietetic habits and the importance of an adequate iodine nutritional status. Statistical analysis: descriptive analysis of all variables will be performed as well as multilevel logistic regression. All analyses will be done carried out on an intention to treat basis and will be fitted for potential confounding factors and variables of clinical importance.

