## Hypothesis

The hygienic-dietetic habits of a pregnant woman has repercussion on both the nutritional status of the mother and the development and growth of the foetus. According to data obtained in a previous study carried out within the Primary Care setting of Catalonia, there is reduced consumption of foods rich in iodine since 71% report eating fish less than three times per week, 18% do not drink milk daily, only 42% use iodised salt for food condimentation and preparation and 18% of the pregnant women surveyed continue to smoke during gestation. We therefore consider that:

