### 1st HYPOTHESIS

Most pregnant women in Catalonia have hygienic-dietetic habits which involve reduced intake of foods containing iodine (such as the eating of fish and the use of iodised salt for food condimentation) and in addition, an important percentage of these women continue to smoke during gestation.

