### Secondary Objectives

1. Validate the questionnaire on nutritional iodine status in pregnant women.

2. Determine the iodine-rich foods consumed by pregnant women in each trimester of gestation and how these foods are prepared (boiled, fried, baked...).

3. Determine whether pregnant women use iodised salt in the preparation and condimentation of foods.

4. Determine whether pregnant women take any supplement containing iodine during gestation.

5. Describe the modifications in the smoking habits produced during gestation.

6. Compare the nutritional iodine status of the pregnant population between the different Primary Care Centres (PCC) participating in the study, ethnic groups, levels of education and gestational trimester.

7. Study the repercussions of the educational interventions on hygienic-dietetic habits and smoking as well as on iodurias and the taking of iodine supplements.

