### Data Collection

*Dependent Variables*: iodine deficiency (yes, no), is defined as ioduria less than 150 μg/lL

Independent Variables:

Variables related to the woman (information obtained through a individualized interview):

- Administrative: PCT, midwife, data collection date, patient code, telephone number.

- Sociodemographic: date of birth, level of education, etnia.

- Obstetric: n° of pregnancies brought to term; n° premature births, n° of miscarriges and n° of live births, trimester of gestation of the woman (1st, 2nd or 3rd).

- Related to smoking: smoker (no, yes), cigarettes/day prior to gestation, cigarettes/day during gestation, ex-smoker because of pregnancy, ex-smoker and time since cessation of smoking.

- Related to consumption of iodine-rich foods:

▪ Consumption of milk: glasses/day

▪ Consumption of yoghourt: units/week and type (whole or skimmed).

▪ Consumption of cheese: rations/week and type (cured, semi-cured and fresh).

▪ Consumption of vegetables: times/week, usual preparation (raw, fried, grilled/baked, steamed, boiled) and use of water in which they have been boiled (yes, no and no answer).

▪ Consumption of vegetables and garden produce: times/week.

▪ Consumption of fish: times/week, usual preparation (raw, fried, grilled/baked, steamed, boiled).

▪ Consumption of tinned tuna: times/week.

▪ Consumption of tinned sardines: times/week.

▪ Consumption of meat and derivatives: times/week.

▪ Consumption of eggs: units/week.

▪ Consumption of fruit: units/week and types (strawberries, pineapple, peaches, bananas, oranges and others).

▪ Consumption of nuts: times/week.

- Consumption of iodised salt: yes (time of consumption), no.

- Consumption of multiple vitamins containing iodine: yes (type), no.

- Consumption of potassium iodine supplement: yes (type), no.

- Related to the intervention: study group (intervention, non intervention), attendance to group workshop (yes, no).

Variables related to the midwife (information obtained through a individualised interview): years in the profession, primary care nursing training, mean number of visits per day.

Variables related to the PCT (information obtained through an individualised interview): population assigned, mean age of population assigned, whether or not it is a teaching center for residents, number of midwives.

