### Statistical analysis

Data will be analysed in concordance with the Consort Cluster guide [44], and all analyses will be done on an intention to treat basis. A descriptive analysis and an analysis of baseline comparability between the study groups will be performed for the variables studied. A Student's t test or a Mann-Whitney U test will be used to compare means with two categories. An ANOVA test will be done to compare means with two or more categories, and a Chi- squared test or a Chi -squared tendency test will be done to compare categorical variables. A multilevel logistic regression will be carried out to evaluate the association between the dependent and the independent variables that were statistically significant in the bivariate analysis. All analyses will be adjusted for potential confounding factors and for variables with clinical relevance. All tests will be done with a 95% bilateral confidence interval. SPSS 15, STATA 10 and HLM6 will be used.

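### Food consumption is named as a trial outcome but handled only as a predictor, so the effect on habits has no endpoint or clustered model, and hypothesis 1 has no criterion

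*Protocol article*

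**What the plan says.** The places that bear on the role of consumption do not agree.

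- **Abstract, Methods/design.** Two outcomes are named: "Outcome measures: consumption of iodine-rich foods and iodine deficiency".
- **Hypothesis 1.** The claim is "Most pregnant women in Catalonia have hygienic-dietetic habits which involve reduced intake of foods containing iodine", with fish and iodised salt given as examples. General objective 1 is to know these habits over the three trimesters.
- **Secondary objective 7.** The aim is to "Study the repercussions of the educational interventions on hygienic-dietetic habits and smoking as well as on iodurias", and on supplement use.
- **Data Collection.** There is one dependent variable: "iodine deficiency (yes, no), is defined as ioduria less than 150" μg/L. The block headed "Related to consumption of iodine-rich foods" stands under the independent variables. It holds 12 food items in different units (glasses a day, units, rations or times a week). Iodised salt and supplements follow in the same list, as does study group.
- **Statistical analysis.** The multilevel logistic regression is there "to evaluate the association between the dependent and the independent variables that were statistically significant in the bivariate analysis". All analyses are also to be adjusted for confounders and clinically relevant variables.
- **Sample size calculation.** The trial is sized on iodine deficiency. The text assumes at least a 15% improvement in habits and, as a consequence, in ioduria.
- **Hypothesis, introductory paragraph.** An earlier study in the same setting is cited: "71% report eating fish less than three times per week, 18% do not drink milk daily, only 42% use iodised salt".

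**The concern.** A variable cannot be both a trial outcome and only a predictor of the other outcome. Three things follow if the methods are applied as they stand.

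1. The effect of the workshop on habits has no defined endpoint, and the only model that handles clustering is not assigned to it.
2. Consumption measured after the workshop may be put into the deficiency model next to study group. If the workshop acts by changing habits, that removes part of the effect the trial was sized to detect.
3. Hypothesis 1 speaks of most women and of reduced intake, but does not say what intake counts as reduced or how several foods are combined. Deficiency, by contrast, has a fixed cut-off.

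**Working it through.** **Plan's own figure first.** The sample size reproduces, and it concerns deficiency only. For 44% against 29%, two-sided 5%, 80% power, with continuity correction, n = 173.6 per group. Dividing by 1 − 0.15 gives 204.2 (stated: 204). The design effect is 1 + (25 − 1) × 0.05 = 2.2. Then 408 × 2.2 = 897.6, so 898 women, and 898 / 25 = 35.9, so 36 teams. None of this is in dispute.

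**Route of consumption through the analysis.** Data Collection makes consumption an independent variable. Statistical analysis admits independent variables that are significant in the bivariate step. If habits do drive ioduria, the consumption items are the ones most likely to be significant, so the better the assumed mechanism holds, the more likely they are to be selected. The section does not say from which trimester the items are taken. First-trimester answers are collected before any education and are harmless as covariates; second- and third-trimester answers are not. The size of the resulting dilution cannot be computed from the article.

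**Hypothesis 1 under different criteria.** The inputs are the earlier-study percentages in the Hypothesis section: fish less than three times a week 0.71, no daily milk 0.18, no iodised salt 1 − 0.42 = 0.58. Most is read as more than 50%.

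| Criterion for reduced intake | Share of women | Most? |
|---|---|---|
| Fish alone | 71% | yes |
| No iodised salt alone | 58% | yes |
| Fish or salt | at least max(0.71, 0.58) = 71% | yes |
| Fish and salt | from 0.71 + 0.58 − 1 = 29% to min(0.71, 0.58) = 58%; 0.71 × 0.58 = 41% if independent | undecided |
| Milk alone | 18% | no |
| All three | at most 18% | no |

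The bounds need no assumption; the 41% assumes independence. Sampling error does not explain the spread. With 898 women and design effect 2.2, p ± 1.96 × √(p(1 − p) × 2.2 / 898) gives 66.6% to 75.4% for fish and 14.3% to 21.7% for milk.

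**The assumed 15% improvement in habits.** Neither the habit nor the scale is stated. Taking the earlier-study figures as control rates, the n per group for 80% power, before loss and clustering and without continuity correction, is:

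| Habit | 15 percentage points | 15% relative |
|---|---|---|
| Fish | 161 (71% to 56%) | 311 (71% to 60.35%) |
| Iodised salt | 174 (42% to 57%) | 979 (42% to 48.3%) |
| Milk | 65 (18% to 3%) | 2988 (18% to 15.3%) |

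The planned trial is equivalent to about 204 × 0.85 = 173 women per group. If the ICC of 0.05 also held for habits, power would be about 83% (fish) and 80% (salt) for 15 points, but 55% and 22% for 15% relative.

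**The case against.** A fair defence is that consumption is largely a descriptive aim. General objective 1 is to know habits, the effect on habits is only secondary objective 7, and the trial is sized on deficiency alone. An article may leave scoring to a fuller document, and the questionnaire is still to be validated against ioduria. The Discussion also promises that the design effect will be accounted for in all main analyses. This stands as far as the absence of a detailed score goes. It does not remove the conflict between the abstract and Data Collection, and the article does not say whether a comparison of habits is a main analysis.

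A reader might infer more than the article supports:

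- *That the effect on habits could be answered either way from the protocol's figures.* No expected or arm-level figure is given for any single habit. All that can be said is that endpoint and scale are undefined.
- *That hypothesis 1 cannot fail.* The two habits it names, fish and iodised salt, each support it when taken alone. A contrary or open answer needs milk, which it does not name, or a combination rule.
- *That false positives are near certain.* Twelve independent tests at 5% would give 1 − 0.95^12 = 46% for at least one, and 24 would give 71%. The plan does not commit to these tests, and answers from the same women are not independent.
- *That women report to the person who delivers the randomised intervention.* Coordinating midwives run the workshop. The interviewing midwife gives the individual education, which both arms receive.

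**Conclusion.** The point holds as an internal contradiction with consequences for the analysis. One of two stated outcomes has no place as an outcome in the methods, no cluster-adjusted comparison is assigned to it, and it may be conditioned on in the deficiency model. That last point rests on the article's own expectation that the workshop acts through habits, and on follow-up rather than first-trimester answers being entered. Hypothesis 1 lacks a criterion: the share of women with reduced intake runs from 18% to 71% across the single habits cited, and from 29% to 58% for the two named habits together. This assumes that the earlier-study percentages apply to the trial population. The definition of iodine deficiency and the sample size are unaffected, so the matter is worth correcting before analysis but does not undermine the trial.

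**What to change.** In Data Collection, list consumption as a second dependent variable, marked as secondary. Base it on a small set of items fixed before analysis; the fish and iodised salt habits named in hypothesis 1 are the natural choice. The cut-offs quoted in the Hypothesis section, such as that behind "71% report eating fish less than three times per week", are one option. State whether each habit is assessed singly or in combination, and use the same rule to test hypothesis 1.

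In Statistical analysis:

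- compare these items between arms at the second and third trimester in the same multilevel logistic model;
- state that follow-up consumption is not a covariate in the model for the intervention effect on deficiency (it may still be studied in a separate model of factors associated with deficiency);
- report the other foods descriptively.

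The sample size section should say which habit the 15% refers to and on what scale.

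A composite such as failing two of three (fish, milk, salt) is not recommended without further thought. If the habits were independent it would hold for 0.71 × 0.18 × 0.42 + 0.71 × 0.82 × 0.58 + 0.29 × 0.18 × 0.58 + 0.71 × 0.18 × 0.58 = 49.6% of women, right at the boundary for most.

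The cost is small: wording and one further model, with all items already collected. The downside is that foods outside the fixed set get no formal test, and that the trial was not powered on consumption.

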## Objectives

### General objective 1

o know the hygieninc-dietetic habits with respect to the consumption of iodine-rich foods and smoking of women during the three trimesters of gestation.

### General objective 2

To know the prevalence of ioduria less than 150 μg/L (iodine deficiency) and the factors associated with its appearance during the first three months of gestation.

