### Sample size calculation

The sample size has been calcuated by multipying the size of a randomized simple design by the design effect. For the simple randomized design an alpha error of 0.05 and a beta error of 0.20 in a bilateral contrast are considered, requiring 204 pregnant women in the intervention group and 204 in the non intervention group to detect a difference greater than or equal to 15% in the prevalence of iodine deficiency between the two. After extensive review of the literature on group educational interventions in a pregnant population, the investigative team [37-40] considered that the intervention to be undertaken in the intervention group will achieve an improvement of at least 15% in hygienic-dietetic habits and thus in the levels of ioduria. A proportion of iodine deficiency of 44% in the non intervention group is assumed as indicated by studies performed in populations in the Pyrenees and the coast of the Maresme, areas near the study setting [18]. A loss to follow up of 15% has been estimated. Using an intracluster correlation coefficient of 0.05 [41-43], and based on an average of 25 pregnant women per PCT, the design effect is 2.2. Therefore, 898 pregnant women and 36 PCT are needed.

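### The between-arm comparison that sets N = 898 is only a secondary objective with no post-workshop time point, and the role of the pre-workshop first-trimester ioduria is left open

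*Protocol article*

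**What the plan says.** All references are to the protocol article.

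- **Outcomes and occasions** (Abstract, Methods/design): "Outcome measures: consumption of iodine-rich foods and iodine deficiency. Points of assessment: each trimester of the gestation".
- **Order of events** (Description of the Study): the first ioduria is requested in both groups in Phase 4, at the initial evaluation. The group workshop is Phase 5, in the intervention group only and also in the first trimester. Interviews and ioduria are repeated in the second and third trimesters (Phase 6).
- **Outcome definition** (Data Collection): deficiency is ioduria below 150 μg/L, yes or no, with no time point. The independent variables include study group and, among the obstetric items, "trimester of gestation of the woman (1st, 2nd or 3rd". First-trimester ioduria is not listed among them.
- **Objectives**: general objective 1 describes habits. General objective 2 concerns the prevalence of deficiency and "the factors associated with its appearance during the first three months of gestation". The effect of the intervention is the last of seven secondary objectives: "Study the repercussions of the educational interventions on hygienic-dietetic habits and smoking as well as on iodurias", together with the taking of supplements. No time point is given.
- **Sample size calculation**: with two-sided alpha 0.05 and power 0.80, each arm needs 204 women before the design effect is applied. The target is "to detect a difference greater than or equal to 15% in the prevalence of iodine deficiency between the two". On the control rate: "A proportion of iodine deficiency of 44% in the non intervention group is assumed". No trimester is attached to either figure.
- **Statistical analysis**: a multilevel logistic regression with the independent variables that were significant in bivariate tests, a general clause on adjustment for confounders and clinically relevant variables, and a baseline comparability analysis. The time structure of the model is not described.

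**The concern.** The trial is randomised and sized to compare two arms, but the objectives rank that comparison below two descriptive ones, and nothing says at which visit it is made. Three visits supply the outcome. By the order of phases, one of them precedes the workshop, and any arm difference there cannot be the workshop's doing.

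Three things follow.

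1. If the three visits were put into one model with a single study-group effect, the pre-workshop visit would pull that effect towards zero.
2. If visits are analysed separately, there is no rule for which one is the result of the trial.
3. The first-trimester value is the natural baseline for a later value of the same variable, and it could correct chance imbalance between only 36 clusters. As written, a variable enters the model through bivariate significance or an unspecified general clause, so its use is not assured.

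The stated time frames also disagree. General objective 2 speaks of the first three months, the abstract's second aim of pregnancy as a whole, and the abstract's methods of every trimester.

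**Working it through.** **Inputs from the documents:** two-sided alpha 0.05, power 0.80, control rate 44%, difference 15 points (44% vs 29%), loss 15%, intracluster correlation 0.05, 25 women per team, N = 898.

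**Step 1: reproduce the plan's figure.** With mean rate 0.365:
- n = [1.96·√(2·0.365·0.635) + 0.8416·√(0.44·0.56 + 0.29·0.71)]² / 0.15² = (1.3345 + 0.5660)² / 0.0225 = 160.5, so 161 per arm.
- With continuity correction: (160.5/4)·[1 + √(1 + 4/(160.5·0.15))]² = 173.6, so 174 per arm.
- After loss: 173.6/0.85 = 204.2, which matches 204.
- Design effect: 1 + 24·0.05 = 2.2. Then 408·2.2 = 897.6, so 898, and 898/25 = 35.9, so 36 teams.

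The arithmetic holds, and 15% must mean percentage points: a relative 15% (44% to 37.4%) would need about 870 to 900 per arm.

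**Step 2: power at one post-workshop visit.** Effective n per arm = 898·0.85/(2·2.2) = 173.5. Power = Φ[(0.15·√173.5 − 1.3345)/0.6725] = Φ(0.953) = 83%. The N suits a single post-workshop contrast.

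**Step 3: what pooling would do.** This model is supplied for illustration; the documents do not state it. With a true effect of 0 at the first trimester and 15 points at the next two, equally weighted: (0 + 15 + 15)/3 = 10 points. In odds ratios, 44% vs 29% is 0.52 and 44% vs 34% is 0.66.
- At single-visit precision, power for 10 points is 48%. The N needed would be 373/0.85·2·2.2 = 1,931, against 833 for 15 points by the same formula (no continuity correction in either).
- Averaging visits also adds precision. With within-woman correlation ρ (not in the documents; assumed 0.2 to 0.8), the variance factor is (1+2ρ)/3 for three visits and (1+ρ)/2 for two:

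| Assumed ρ | Three trimesters, 10 points | Second and third only, 15 points |
|---|---|---|
| 0.2 | 80% | 97% |
| 0.5 | 65% | 92% |
| 0.8 | 54% | 87% |

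These figures apply the same design effect to averages and an unpooled variance (84% rather than 83% at a single visit).

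**Step 4: choosing the visit afterwards.** Taking the better of two post-workshop tests at 0.05 gives a false-positive rate between 5% (tests perfectly correlated) and 1 − 0.95² = 9.75% (independent).

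**Step 5: baseline adjustment, illustrative only.** Dividing 173.5 by (1 − r²) with assumed r = 0.3 to 0.5 gives 191 to 231 per arm and power of 86 to 92%. This is a linear-model factor applied to a clustered binary outcome. Between-cluster variance makes up 0.05/(0.05 + 0.95/25) = 57% of the variance of a team mean, so the real gain depends heavily on a cluster-level correlation that the documents do not give.

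**The case against.** The strongest reply is that the document never says the trimesters are pooled. A reader might infer from the abstract's three points of assessment, and from trimester and study group appearing together as independent variables, that the workshop effect will be diluted. The text does not support that. The Statistical analysis section names a multilevel logistic regression without its time structure, and an analysis by visit or with a group-by-trimester term fits equally well and would not be diluted. The Data Collection list is a catalogue of items (it includes patient code and telephone number), not a model. This stands: dilution is a possibility left open, not a planned result.

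A reader might also infer that first-trimester ioduria is excluded as a covariate. That too goes beyond the text. The clause on clinically relevant variables could admit it, and a fuller plan may name it.

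Measuring ioduria in the first trimester is, moreover, legitimate. It serves the prevalence objective, and Phase 4 ties the start of any supplementation to the first urine sample so that first-trimester prevalence is not distorted. The reference to the first three months in general objective 2 may be a slip for three trimesters.

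None of this answers the core. Objectives, outcome definition and sample size target are protocol content, they are stated here, and they do not agree on which comparison comes first or when it is made.

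**Conclusion.** The point holds in this form: the comparison that determines N = 898 is ranked only as secondary objective 7, has no stated post-workshop time point, and leaves the role of the pre-workshop ioduria unfixed. The sample size is not wrong; it gives about 83% power for 44% versus 29% at one post-workshop visit.

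The size of the risk depends on the analysis eventually chosen. Equal-weight pooling would take 15 points to 10, with power of about 54 to 80% against 87 to 97% for the second and third trimesters alone, under assumed correlations of 0.8 to 0.2. At the lowest assumed correlation the pooled power is close to that of a single visit, but the estimate would still understate the post-workshop effect. An analysis confined to a post-workshop visit, or with a group-by-trimester term, loses nothing. No firm figure can be put on the gain from baseline adjustment.

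That the first sample precedes the workshop rests on the order of Phases 4 and 5; both fall in the first trimester, and the article does not state the order for each woman. The wording should be changed before analysis. It does not invalidate the design.

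**What to change.** 1. Name the between-arm comparison of iodine deficiency at one stated post-workshop trimester as the primary intervention analysis, and tie the 44% and the 15 points to that visit. Second or third trimester is the sponsor's choice; nothing in the document makes one of them right.
2. Exclude the first trimester from the outcome occasions of that model. Keep it for the descriptive prevalence objective. If both later visits are modelled together, include a group-by-trimester term.
3. Enter first-trimester ioduria as a pre-specified baseline covariate in the multilevel logistic model, whatever its bivariate significance. State that the sample is collected before the workshop, and that the adjusted odds ratio is conditional on this covariate.
4. Reconcile the time frame in general objective 2 with the abstract's aim and its points of assessment.

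Cost: wording in the objectives, outcome, sample size and analysis sections. All the data are already to be collected and N does not change.
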